### Participant allocation

Sequence generation and randomization will be via a centrally controlled web-based GCP compliant randomization system, run by Tayside Clinical Trials Unit (TCTU). Randomization will be stratified by site. To ensure balanced assignment across critical variables, a minimization algorithm will be employed, using baseline age.

Participants will receive the intervention or the control as per randomization schedule.

Stratification will be by age, into two groups: 7 and 8 years and 9, 10, and 11 years.

### Blinding

Due to the nature of the proposed intervention it is not possible to blind staff, the children or their carers to the group once it has been allocated.

### Data collection, management and analysis

#### Primary outcomes

The primary outcome measure is extent of tipping of the lower second permanent molar, with a favorable outcome being a degree of tipping less than 15° and unfavorable outcome being greater than 15°.

Participants will be allocated into ‘favorable’ or ‘unfavorable’ outcome groups when comparing study models.

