### Target sample size

The sample size calculation is based on the primary outcome of tipping of the lower molar tooth. There are no published data on which to base the calculation, therefore local audit data were used. These data indicated that tipping of the molar (a dichotomous outcome of either less than or more than 15 degrees tipping in the vertical direction) lies somewhere between 50:50 and 60:40 for good to poor outcome in a representative group. A finding of a difference in this proportion of 10 percent between the two groups, for example proportions of 50:50 and 40:60, in the two comparison groups would be deemed to be clinically significant.

Sample size calculation for a power of 0.8 and an alpha of 0.05 indicated a sample of 124 in each group if the true population proportion is 60:40, or 171 if the proportion is 50:50. It was therefore decided to set the required sample size at 150 in each group, requiring 300 in total. Allowing for a drop-out rate of 25% our target sample size is therefore 400.

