**Other clinical records**			
Dental impressions and occlusal registration	**X**	**X**	**X**

At time of extraction (T0):

1. Dental impressions and a record of occlusal registration will be taken for study models

2. The dentists will complete a case report form (CRF) (patient details, which arm randomized to, which side treatment was allocated to, what kind of anesthetic was used - local anesthesia (LA)/inhalation sedation (IHS)/general anesthesia (GA)/other type of sedation)

3. Children’s Oral Health-Related Quality of Life (OHRQoL) questionnaire

4. Parental OHRQoL questionnaire

After 1 year (T1):

1. Dental impressions and a record of occlusal registration will be taken for study models

2. Record of any dental treatment (to remaining upper FPMs) or orthodontic treatment provided since initial intervention

3. Children’s OHRQoL questionnaire

4. Parental OHRQoL questionnaire

After 5 years or when child turns 14 (whichever is first) (T2):

1. Dental impressions and a record of occlusal registration will be taken for study models

2. Dentists will record any dental treatment (to remaining upper FPMs) or orthodontic treatment provided since initial intervention

3. Children’s OHRQoL questionnaire

4. Parental OHRQoL questionnaire

The CRFs and questionnaires will all be marked with the patient’s unique study ID number which will be linked to the enrollment log for the trial.

Study models will be 3D scanned to measure occlusal changes. All patients’ lower study models will be assessed with regard to the tipping of the lower second permanent molar relative to the occlusal plane. The scanning software will be able to create an occlusal plane from cusp tips in order to calculate the degree of molar tipping. Not all patients will have an erupted lower second permanent molar at the earlier time points in the study.

Only the groups of patients who do not have the upper FPMs extracted will require their upper study models to be assessed for FPM over-eruption. Each patient’s upper models will be superimposed on the palatal rugae and any movement in the *x, y* and *z* plane of the upper FPMs will be recorded.

In addition, the 3D scans of the models will be used to give ABO occlusal index scores and to assess and measure any residual spacing between the lower second permanent molar and the lower second premolar.

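### The primary comparison cuts a scanned tipping angle at 15°, near the middle of its distribution, although analysing the angle itself would probably give more power at little cost

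*Protocol article*

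**What the plan says.** The Primary outcomes section names the extent of tipping as the primary measure and then fixes two categories, "with a favorable outcome being a degree of tipping less than 15° and unfavorable outcome being greater than 15" degrees. It adds: "Participants will be allocated into ‘favorable’ or ‘unfavorable’ outcome groups when comparing study models". Target sample size rests on the same split, described as "a dichotomous outcome of either less than or more than 15 degrees tipping in the vertical direction".

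The text under Data collection shows that a number will exist behind the category. "Study models will be 3D scanned to measure occlusal changes", and the software will "create an occlusal plane from cusp tips in order to calculate the degree of molar tipping".

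On where the cut falls, Target sample size reports from local audit that the outcome "lies somewhere between 50:50 and 60:40 for good to poor outcome in a representative group". It treats a 10-point difference between groups as clinically significant.

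Data management and statistical methods lists the degree of tipping among the between-group comparisons, without the 15° cut. It allows parametric or non-parametric methods, but does not say that this comparison is the primary one.

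**The concern.** A cut near the median keeps only which side of 15° a molar falls on. Molars at 14° and 16° become opposite outcomes, while 16° and 40° become the same outcome. The size of the shift within each category plays no part in the primary test.

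This matters more than usual here. The outcome is read at five years or age 14, and 150 evaluable children per group is well short of what a 10-point difference in proportions needs. Information already collected by the scan is cheaper than more recruitment. The definition also leaves a reading of exactly 15° in neither category.

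**Working it through.** **Inputs from Target sample size:** power 0.80; alpha 0.05 (sidedness not stated, two-sided taken); favorable proportion 0.50 to 0.60; difference 0.10, with 0.50 versus 0.40 as the worked example; 150 per group, 300 in total, 400 after 25% dropout.

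**1. The plan's own figures.** Dropout reproduces: 300/0.75 = 400. The sizes of 124 and 171 per group do not. With p̄ the mean of the two proportions,

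n = [1.96√(2p̄(1−p̄)) + 0.842√(p₁(1−p₁)+p₂(1−p₂))]² / (p₁−p₂)²

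- 0.50 v 0.40: (1.96×0.7036 + 0.842×0.7000)²/0.01 = 387.3, so 388 per group
- 0.60 v 0.70: (1.96×0.6745 + 0.842×0.6708)²/0.01 = 355.9, so 356 per group
- One-sided testing still needs 305 or 281.

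**2. Power on the cut at 150 per group.**

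- 0.50 v 0.40: Φ[(0.10×√150 − 1.96×0.7036)/0.7000] = Φ(−0.22) = 41%
- 0.60 v 0.70: Φ[(0.10×√150 − 1.96×0.6745)/0.6708] = Φ(−0.145) = 44%

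**3. Efficiency of the cut if the angle is normal with equal spread (assumption).** Relative efficiency is φ(z_p)²/[p(1−p)]:

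- p = 0.50: 0.3989²/0.25 = 0.637
- p = 0.60: 0.3863²/0.24 = 0.622

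The loss is therefore 36–38%.

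**4. The same effect analysed on a normal angle.** The standardised difference is d = |z(p₁) − z(p₂)|, the size is n = 2(2.80/d)², and power at 150 per group is Φ(d√75 − 1.96).

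| Proportions | d | n per group for 80%, angle | n per group for 80%, cut | Power at 150, angle | Power at 150, cut |
|---|---|---|---|---|---|
| 0.50 v 0.40 | 0.253 | 245 | 388 | 59% | 41% |
| 0.60 v 0.70 | 0.271 | 214 | 356 | 65% | 44% |

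**5. Other shapes.** The protocol gives no mean, SD or shape for the angle, so a range is needed. The loss from the cut, relative to a t-test on raw degrees, is:

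| Shape of the angle | Loss |
|---|---|
| Normal | 36–38% |
| Logistic | 18–21% |
| t with 5 df | about 4% |
| Lognormal, log-SD 0.5 | about 28% |
| Lognormal, log-SD 0.7 | about 18% |
| Lognormal, log-SD 0.9 | about 2% |
| Lognormal, log-SD 1.0 | none; the cut does better |

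A rank-based test behaves differently. In simulation at 0.50 v 0.40 and 150 per group, with the lognormal shift made on the log scale, it has about 50–58% power across all these shapes. The cut has about 42–44% in the same runs.

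**The case against.** The strongest reply is that nothing here is an error. The abstract, Target sample size and Primary outcomes all use one pre-specified 15° outcome, and clinical significance is defined as a difference in proportions. A responder endpoint that clinicians can read is a legitimate choice even when it costs power. That stands: this is an improvement in efficiency, and nothing in the documents shows 15° to be clinically wrong.

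Several stronger readings are tempting and are not supported:

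- **That a third of the information is lost outright.** This holds only under normality, which the documents do not give. Under strong skew a raw t-test gains nothing over the cut.
- **That the angle is thrown away.** Degree of tipping is among the listed comparisons. The issue is which analysis is primary.
- **That every child will have an angle.** Data collection warns that the second molar may be unerupted at the earlier time points, and availability for all at the final visit is not stated. The dichotomy has the same dependence.
- **That reading error near 15° is a special defect of the cut.** No measurement error is reported, and random error weakens an analysis of the angle too.
- **That changing the analysis rescues the trial.** It does not; 150 per group gives 59–65% power even under normality.

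The skew argument tells against a raw t-test. It does not tell against analysing the angle, because the rank-based gain holds in every shape tried and the protocol already allows non-parametric methods.

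**Conclusion.** The point holds as a worthwhile, low-cost improvement to the choice of primary analysis. The trial computes the angle, and the audit data put the cut near the median. With 150 per group and 0.50 versus 0.40, moving from the cut to the angle raises power from about 41–44% to about 50–58% with a rank-based method, or to 59% with a t-test if the angle is normal.

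These figures assume two-sided testing at 0.05, independent children, and a shift between arms of the shapes listed. The documents confirm none of those shapes. A gain is seen in all of them with a rank-based method, but its size is uncertain. The shortfall against 80% power comes mainly from the sample sizes of 124 and 171, which are a separate and larger fault.

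**What to change.** Name the between-arm comparison of the final-visit (T2) angle as the primary analysis, with a method robust to skew: rank-based, ordinal (cumulative probability) regression, or a suitable transformation. Adjust for age group and allow for site, the two factors in Participant allocation.

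Pre-specify the difference in the proportion below 15° as the companion clinical result, either observed or derived from the same model, so that the 10-point difference stays usable. Assign a reading of exactly 15° to one category. Settle all of this before any final-visit data are seen, so that the choice between angle and cut cannot be made after the fact.

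The cost is wording. No visit or measurement is added, but because the primary analysis changes, it should go through the route in Protocol amendments. The downside is that the headline test is on the angle rather than the 15° proportion. It also needs a measurable erupted second molar, as the dichotomy does. The sample size must be corrected separately.

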#### Secondary outcomes

The secondary outcomes for the study are:

1. position of the upper FPMs with regard to over-eruption^a^;

2. residual spacing between the lower second permanent molar and the lower second premolar^a^;

3. American Board of Orthodontics (ABO) scores^a^;

4. type of anesthetic used during procedures^b^;

5. dental or orthodontic treatment carried out during the follow-up period^b^ ;

6. Child and Parent Oral Health-Related Quality of Life (OHRQoL) scores (child and parent questionnaires).

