**Methods/Design:**

This is a multicenter, two-arm parallel group randomized clinical trial. Allocation will be web-based randomization. Practitioners in primary and secondary care settings, reflecting the points of presentation and treatment of eligible patients, will recruit 400 children, aged 7 to 11 years requiring extraction of lower first permanent molars but who have upper first permanent molars of good prognosis. Baseline measures (prior to treatment) and outcome data (at one and five years, or when the patient reaches 14 years of age) will be assessed through study models and child/parent questionnaires.

The primary outcome measure is degree of tipping of the lower second permanent molar, (favorable outcome is tipping less than 15°).

The secondary outcomes are type of anesthetic/sedation used, residual spacing (between lower second premolar and second permanent molar), orthodontic treatment requirement, quality of life, and over-eruption in the intervention group. Assessors will be blinded where possible.

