#### Prevention of mesial movement of mandibular second molar

The Royal College of Surgeons of England (RCS) national guidance document [7] cites Holm [16] as the main data source for supporting compensating extractions following loss of lower FPMs. This paper is a conference report, reviewing 1,119 cases involving loss of one or more FPMs over a 10-year period at the Hamburg Public Orthodontic Institute. The review was carried out principally to assess the proportion of cases involving loss of FPMs, and the patterns of extraction. Although the poorest outcomes were found in cases of uncompensated extraction of lower FPMs, no data were presented to support this. In contrast, Mejare [8] reviewed 32 patients (mean age 18 years) who had loss of one or more FPMs in childhood (mean age 10 years) due to molar incisor hypomineralization (MIH). Of this sample, five patients had an uncompensated extraction of a lower FPM, and in none of these patients was over-eruption of the upper FPM noted. In addition, in a longitudinal study of 27 children who had one or more FPMs extracted due to MIH, Jalevick [17] reported no significant occlusal problems with the four children with uncompensated extractions of lower FPMs, and recommended against the need for compensating extractions. Patient satisfaction was also investigated in this study, and it was reported that of the five children assessed as having need of orthodontic correction of their occlusion, three of them declined treatment as they felt there was no need for it.

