**Case report form to be completed by dentist**			
Baseline demographic information	**X**		
Dental history	**X**		
Record intervention or control arm	**X**		
Record side of treatment (right or left)	**X**		
Record stage of development of lower second molar	**X**		
Record type of anesthetic/sedation used	**X**		
Record dental treatment to remaining upper first permanent molars	**X**	**X**	**X**
Record orthodontic treatment since intervention		**X**	**X**

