#### Orthodontic/dental review

The dentist will complete a questionnaire regarding dental and orthodontic treatment at 1 year follow-up and final follow-up to find out whether:

1. the upper FPM is still present (for participants in the intervention group);

2. the upper FPM has required dental treatment and if so, details of the treatment (for participants in the intervention group);

3. the patient had, or are they currently undergoing, any orthodontic treatment? (If yes, the type of treatment);

4. they have experienced any symptoms of temporo-mandibular joint dysfunction syndrome (jaw pain).

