#### Data management and statistical methods

Anonymized cast models will be 3D scanned and process data analyzed to record the type and extent of dental treatment (including the study interventions) that the subjects have received during the period of the study. This will be entered into a GCP compliant data management system Open Clinica (https://www.OpenClinica.com), which can be exported to SPSS (Statistical Package for Social Sciences, Inc., Chicago, IL, USA) v.18 for statistical analysis. Patient satisfaction questionnaires will be entered into Open Clinica and exported to SPSS for descriptive statistical analysis.

COHQoL data will be entered into Open Clinica and exported to SPSS for quantitative analysis of differences in overall and domain scores at the three time points using Friedman test for repeated measures

For between group comparisons, data will be checked for normality of distribution and any evidence of skewness. Descriptive statistics will be prepared. Appropriate parametric or non-parametric analysis allowing for any clustering effect will be undertaken to determine statistically significant differences in the outcomes listed above between the two study groups including chi-squared and *t*-tests, if normally distributed.

The proposed analyses will investigate comparisons between the intervention group, where patients have not had compensatory removal of FPMs, and the control group where patients have had this done. Specifically, we are looking for clinically significant improvement in:

•position of second permanent molars (if erupted);

•degree of tipping of the lower second permanent molars;

•spacing between lower second premolar and second permanent molars;

•position/over-eruption of upper FPM in the intervention group;

•ABO scores;

•dental/orthodontic treatment required during the study period;

•child OHQoL scores;

•use of anesthetics.

Missing data will be analyzed by multiple imputation up to the patient’s last recorded visit.

Interim analyses will not be carried out for this study as it will not be possible to measure the primary outcome until recordings are taken at 5-year follow-up, by which time patient recruitment will be complete.

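### The orthodontic secondary outcome is named as treatment required, but the listed data items record only treatment received

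*Protocol article*

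**What the plan says.** The protocol article describes this outcome in two ways.

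- **As requirement.** The abstract (Methods/Design) lists "orthodontic treatment requirement, quality of life, and over-eruption in the intervention group" among the secondary outcomes. The section on data management and statistical methods lists "dental/orthodontic treatment required during the study period" among the comparisons between arms.
- **As treatment received.** Item 5 under Secondary outcomes is "dental or orthodontic treatment carried out during the follow-up period", and the endnote says dentists record it on the case report form. Table 1 has the row "Record orthodontic treatment since intervention" at one year and at final follow-up. For the final visit, the Data collection section says: "Dentists will record any dental treatment (to remaining upper FPMs) or orthodontic treatment provided since initial intervention". The questionnaire under Orthodontic/dental review asks whether "the patient had, or are they currently undergoing, any orthodontic treatment" and, if so, its type.

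The background section on mesial movement of the lower second molar describes a cited longitudinal study of 27 children. Five were assessed as needing orthodontic correction, and "three of them declined treatment as they felt there was no need for it".

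**The concern.** Requirement and receipt are different quantities. A child can need orthodontic treatment and not have it because the family declines, because a referral is pending, or because treatment has not yet started. On the items listed, all of these children are recorded in the same way as a child with no need, so requirement cannot be recovered from the data at analysis.

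Final follow-up is at five years or age 14, whichever comes first. A child who enters at 7 is last seen at 12. A child who enters at 11 is last seen on reaching 14, after at most about three years. Some children in need may be untreated at that point simply because of timing.

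At stake is what the trial may say about this outcome. A report that the arms had similar orthodontic requirement would rest on data about uptake, which also reflects family preference and the decisions of dentists who know the allocation.

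**Working it through.** The plan states no figure for this outcome, so there is nothing to reproduce. The check compares the wording, then asks how much can be said about size and direction.

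**Step 1: name against data item**

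| Place in the protocol article | What it refers to |
|---|---|
| Abstract, Methods/Design | requirement |
| Data management and statistical methods | treatment required |
| Secondary outcomes, item 5 | treatment carried out |
| Table 1 | treatment since the extraction |
| Data collection, one year and final visit | treatment provided |
| Orthodontic/dental review | treatment had or under way, and type |

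Two places name requirement. The other four describe receipt, and none has an item for assessed need, referral, waiting or refusal.

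**Step 2: what the cited study can show**

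Inputs from the background section: 5 children in need, 3 declined.

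- Share declining: 3/5 = 60%.
- Exact (Clopper-Pearson) 95% interval: the 2.5% quantile of Beta(3, 3) is 14.7%, and the 97.5% quantile of Beta(4, 2) is 94.7%.
- Uptake among those in need is therefore at most 2/5 = 40%, with interval 5.3% to 85.3%.

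This shows that need and uptake can part. It does not say by how much in this trial.

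**Step 3: illustration with equal uptake in both arms**

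The need rates of 30% and 20% are assumptions, because the protocol gives none. Recorded rate = need × uptake. Power is the normal approximation for two proportions, two-sided alpha 0.05, with the 150 per group from the sample size section.

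| Uptake | Recorded rates | Difference | Power |
|---|---|---|---|
| 100% | 30% v 20% | 10 points | 0.52 |
| 85% | 25.5% v 17% | 8.5 points | 0.44 |
| 40% | 12% v 8% | 4 points | 0.21 |
| 15% | 4.5% v 3% | 1.5 points | 0.10 |

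The loss runs from small to nearly total across uptake values compatible with the cited study.

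**Step 4: illustration with unequal uptake**

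The Blinding section says that staff, children and carers know the arm, so equal uptake cannot be taken for granted. All figures here are assumed.

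- Need 30% v 20%, uptake 40% v 60%: 0.30 × 0.40 = 12% and 0.20 × 0.60 = 12%. A real difference in need disappears.
- Need 20% in both arms, uptake 60% v 40%: 0.20 × 0.60 = 12% and 0.20 × 0.40 = 8%. A difference appears where need is the same.

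The between-arm error can therefore take either direction.

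**The case against.** The strongest reply is that the formal definition is clear. The numbered outcome list says treatment carried out, and every collection item agrees with it. The conflict is with a phrase in the abstract and one bullet in the analysis section, where required might be read loosely as needed and given. This largely stands: the outcome list labels the item correctly, and consistent naming would resolve the contradiction.

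Treatment received is also a legitimate outcome. It reflects burden on the child, and the children who declined in the cited study saw no need. That stands too. The fault lies in calling it requirement.

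Next, occlusal status is measured apart from uptake records. Tipping, residual spacing and American Board of Orthodontics (ABO) scores come from scanned, anonymized models. These measures limit the damage to the trial's overall conclusion. They do not supply requirement: the protocol does not derive need from the ABO score, and a child already treated by the final visit may score well although treatment was needed.

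Finally, the article summarizes a questionnaire that is not shown, and the full form may hold more. If it does, the article should say so. The conflict in naming remains either way.

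A reader might infer that the outcome misses 60% of need, or that it shrinks the difference between arms and makes leaving the upper molar look safer. The documents support neither. The first rests on five children in a study where only four of the 27 had uncompensated lower extractions. The second requires similar uptake in both arms, which an unblinded trial cannot assume: dentists who refer more readily when the upper molar is kept would make that arm look worse. Treatment for reasons unrelated to the extractions would also add to the recorded rate.

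**Conclusion.** The point holds as a mismatch between the named outcome and the data collected. The protocol says it will compare orthodontic requirement, yet its listed items support only a comparison of treatment received. That follows from the text alone and rests on no assumed figure.

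The size of any undercount is not established, nor is the direction of any bias between arms. The fall in power from 0.52 to 0.21 is only an illustration: it assumes need of 30% v 20% and 40% uptake in each arm, for a secondary outcome on which the trial was not sized. The primary outcome is not affected. It is worth correcting because the remedy is cheap and determines whether the trial can say anything about requirement.

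**What to change.** **Minimum.** Call the outcome orthodontic treatment received in the abstract, the list of secondary outcomes and the statistical methods section. This costs only an edit.

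**If requirement is to be reported.** Add two response categories to the existing dentist questionnaire at one year and final follow-up, in both arms: referred or waiting, and assessed as needing treatment but declined. Define requirement as either of these or treatment had or under way. Report it separately from treatment received.

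**Where feasible.** Score a grade of orthodontic need from the anonymized final-visit scans already used for ABO scoring, and report it beside the questionnaire result. Read it together with the treatment record, since a child already treated may show little remaining need.

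**Cost.** A few more form items and some extra scoring of scans already planned. Need reported by the dentist remains an unblinded judgment, which is the reason for the scan-based grade.
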